### Data management

To protect privacy, each study participant is assigned a unique four-digit identification number that cannot be traced to any protected health information (PHI). All data forms, participant information, and biological specimens are coded using these identification numbers. No personally identifiable information (PHI) appears on these materials; instead, the keys linking participants’ identities to their unique identification numbers are stored separately in a secure software system designed for clinical trials which meets both HIPAA and 21 CFR Part 11 requirements.

All study data are managed in a central database using REDCap, a secure web-based software system designed for clinical trials which meets both HIPAA and 21 CFR Part 11 requirements. All questionnaires and daily surveys are coded into REDCap and administered electronically. Data from serum assays, REE measurements, and sensory measures via dermatomal somatosensory evoked potentials and EPTs are output from the respective technical equipment in electronic form and then uploaded directly into the REDCap database. However, data on adverse events that are collected by the medical team are recorded on paper forms, stored in the clinical research unit, and then manually entered into the REDCap database. Neurological data (assessed by ISNCSCI standards) and food intake data are captured on paper forms and double entered into the database.

Paper documents are scanned and saved on UAB’s secure network and/or stored in locked cabinets in the research coordinator’s office. The PI and postdoctoral trainee periodically check the database for missing data and document all such data and the reasons for absence. The study statistician also periodically performs a quality check of the database, which includes error checks using expected ranges for data values. After the study has completed, all data quality will be checked by the statistician, PI, and the postdoctoral trainee in year 3; tasks are divided among the three personnel according to their respective responsibilities. In compliance with UAB Institutional Review Board (IRB) policies, all data and records will be kept for at least 3 years after the study is completed; all PHI for participants will be deleted 3 years after the trial is completed, while the deidentified final dataset will be retained indefinitely and published online for other scientists to benefit from.

### Statistical analysis

Statistical analyses for neurological recovery will include comparisons of means of motor and sensory function, functional independence and serum measurements (e.g., glucose, insulin, alanine aminotransferase and aspartate transaminase) between the two groups, as well as comparisons within each group of the changes from baseline to rehabilitation to discharge (which should take approximately 5 weeks). Descriptive statistics, including measures of central tendency (sample mean, sample median) and dispersion (variance) will be calculated for each group. For safety outcomes, instead of comparing the two groups to the established standard safety values, we will compare circulating levels of proposed outcomes at the various time points among the two groups. If there are no significant group differences in these outcomes, we will conclude that the KD intervention is safe. We will also calculate 95% confidence intervals for the mean group differences for these outcomes as an additional check on safety and feasibility. The primary method of analysis will be analysis of covariance (ANCOVA), regressing the 5-week outcomes (safety, motor and sensory recovery, functional independence, and glycemic state) on the randomly assigned diet, baseline values of the measures, and other covariates such as age and sex. Repeated measures ANCOVA will also be used. Statistical assumptions will be assessed using box plots, residual plots and normal probability plots. Secondary analyses, accounting for all time points, will be conducted using mixed linear models, including repeated measures models. An appropriate structure for the covariance matrix (e.g., the unstructured covariance matrix) will be selected for these models using the final data. When a model term is statistically significant, the Tukey–Kramer multiple comparisons test will be used to determine which specific pair of means are significantly different. This method will allow us to compare changes over time (within-group changes) and differences between groups simultaneously. Covariates (e.g., length of enteral and solid feeding and length of stay in acute and rehabilitation care) will be accounted for in these analyses. Overall cross-sectional between-group comparisons, such as baseline comparisons used to examine pretest parameters, may be performed using the two-group *t* test, and overall within-group comparisons may be performed using the paired *t* test. If assumptions of normality of distribution for the above tests are not tenable, variables may be transformed prior to analysis, or appropriate nonparametric tests, such as the Wilcoxon rank-sum and signed-rank tests, may be used. Statistical tests will be two-sided and will be performed using a 5% significance level. Stratified analyses accounting for different injury levels will also be performed. These analyses will be specific to the distribution of data in each individual subgroup, which will minimize heterogeneity and allow us to analyze subgroups that may be more statistically homogenous and clinically relevant. SAS software, version 9.4 or later, will be used to conduct the statistical analyses. Multiple imputation methods will be used to address missing data for variables with moderate amounts of missing data (≥10%) and after examining whether data are missing completely at random, missing at random, or missing not at random. Missing data analysis will not be performed on variables with <10% missing data to avoid statistical bias larger than that obtained through the use of complete case analysis.

For microbiome analysis, alpha diversity indices will be analyzed using linear mixed-model with time (pre- and post-) and group (KD and SD) as fixed factors and participant as a random effect. Permutational multivariate analysis of variance testing will be used to assess the effects of time, treatment, and time × treatment on beta diversity indices. The principal coordinate analysis will be performed to visualize the beta diversity distance matrices [18].

For targeted proteomics, three specific analytic approaches will be utilized. First, two-sample *t* tests, or Wilcoxon rank-sum tests if the normality assumption is questionable, will be used to examine differences in the number of selected peptides and proteins between diet groups at discharge (approximately 5 weeks). Because of the number of proteins to be examined, a false discovery rate of 0.2 will be used to account for multiple hypothesis tests. The second approach will examine the manner in which levels of selected peptides vary across the longitudinal time points of baseline, rehabilitation and discharge. To examine these patterns, mixed linear models such as repeated measures models using time as a within-person factor and diet as a between-person factor will be constructed. Finally, Pearson’s correlation will be used to measure the strength and direction of linear associations between selected peptide levels and 5-week outcomes of safety, neurological, functional and glycemic status. 

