## Outcome measures and analysis

The primary outcomes are as follows: 1) safety via biomarkers of systemic inflammation (C-reactive protein), lipids (total cholesterol, high-density lipoprotein cholesterol, low-density lipoprotein cholesterol and triglycerides), sodium, liver enzymes (alanine aminotransferase, aspartate transaminase, alkaline phosphatase, albumin, bilirubin, total protein, nutritional ketosis (β-hydroxybutyrate) and glycemic status (fasting blood glucose and insulin)); 2) neurological recovery (AIS) motor and sensory scores and EPTs; 3) functional independence (SCIM); 4) microbiome composition; and 5) serum biomarkers (targeted proteomics).

In compliance with goals of the National Institute of Neurological Disorders and Stroke common data elements initiative, we are utilizing portions of the SCI common data elements that are expected to increase the efficiency and effectiveness of our clinical research study and diet intervention, increase data quality, and facilitate data sharing and comparisons across studies. For data analyses and results reporting, we adhere to the guidelines for reporting results using the international spinal cord core dataset [28].

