### Minimally acceptable intervention adherence rates

Adherence to diet will be closely monitored by the study team by measuring serum β-hydroxybutyrate levels once a week. A blood concentration of 0.5–3 mM (nutritional ketosis) will be considered safe and acceptable. Adherence will also be assessed using food records. The food record will be a simple checklist to indicate that supplied foods were consumed, with space to add the quantity of consumption and any deviations from the protocol. In addition, the study dietician will communicate directly with each participant at least weekly to improve adherence.

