### Trial monitoring

No regular external trial auditing is scheduled. However, the Data and Safety Monitoring Committee (DSMC) includes two external safety monitors and three study personnel including the PI, study physician and a postdoctoral fellow. Key investigators and study staff provide the DSMC with information regarding safety end points, data quality and validity every 3 months over the course of the study. All human participant data, ranging from recruitment/screening to diet intervention and testing to laboratory tests, are reviewed every 3 months by key study staff, the PI and the DSMC. This includes updates on any new hazards, risks or adverse events, and plans of action. Additional investigators and staff will be asked to participate as the need for their input or expertise arises. If during the course of these meetings particular unforeseen hazards or risks are identified that may predispose to an unusually high number of serious adverse events, the PI consults the appropriate members of the investigative team, as well as the UAB IRB and National Institutes of Health (NIH)/National Institute of Nursing Research (NINR) to determine if the study should be terminated or altered in some way. Any procedure that is deemed hazardous is eliminated from the study and replaced with an alternative if one with reasonable risk can be identified.

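### The safety conclusion rests on group levels alone, so the diet could be called safe despite several severely abnormal KD patients

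*Protocol article*

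**What the plan says.** The Outcome measures and analysis section lists safety first among the primary outcomes. Its markers are C-reactive protein, four lipids, sodium, six liver-panel measures, β-hydroxybutyrate, glucose and insulin.

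The Statistical analysis section says how they will be judged:

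- The comparison: "For safety outcomes, instead of comparing the two groups to the established standard safety values, we will compare circulating levels".
- The conclusion: "If there are no significant group differences in these outcomes, we will conclude that the KD intervention is safe".
- The supplement: "We will also calculate 95% confidence intervals for the mean group differences for these outcomes as an additional check on safety and feasibility".
- The primary model is ANCOVA, "regressing the 5-week outcomes (safety, motor and sensory recovery, functional independence, and glycemic state) on the randomly assigned diet", with baseline and other covariates. If normality fails, "appropriate nonparametric tests, such as the Wilcoxon rank-sum and signed-rank tests, may be used".

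Other sections look at individual patients. Under Trial monitoring, all participant data including "laboratory tests, are reviewed every 3 months by key study staff, the PI and the DSMC". Adverse events go to the IRB. Data management has range checks for data quality. Under Minimally acceptable intervention adherence rates, a ketone range of 0.5–3 mM is treated as safe. None of these is linked to the safety conclusion.

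**The concern.** ANCOVA, the t test, the rank-sum test and the interval for the mean difference all describe where a group lies. Drug or diet toxicity in laboratory markers usually appears in a few patients, while the rest of the arm stays normal. Those few patients raise the arm's variance along with its mean, so the test statistic moves little. Sodium is harmful in both directions, and low and high values cancel in the mean.

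This is a separate problem from treating non-significance as proof of safety. Even a mean difference known exactly to be zero would not exclude several severely abnormal KD patients, so a margin or a tighter interval on the mean would not cure it. At stake is a published statement, on the first-listed primary outcome, that the diet is safe.

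**Working it through.** **Inputs from the article.** There are 24 completers per arm (Power calculations), and tests are two-sided at 5% (Statistical analysis). The article's own power figures reproduce: a difference of 19.5 with SD 23.5 gives 80.3%, and 27.3 with SD 33 gives 80.1%. This corresponds to a detectable shift of 0.83 SD. No margin, distribution or power is given for any safety marker.

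**Assumed inputs.** ALT is log-normal with median 30 and log-SD 0.6; affected KD patients are set to 200. Sodium is normal with mean 140 and SD 3; affected patients are set to 125 or 155. The baseline correlation for ANCOVA is 0.5. Each scenario used 20,000 simulated trials.

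**Why ALT is missed (3 of 24 KD patients).**

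- Unaffected mean = 30 × exp(0.6²/2) = 35.9; variance = 35.9² × (exp(0.36) − 1) ≈ 559.
- Expected mean difference = (3/24) × (200 − 35.9) = 20.5.
- KD variance ≈ 0.875 × 559 + 0.125 × 0.875 × 164.1² ≈ 3,434.
- Standard error ≈ √((559 + 3,434)/24) = 12.9.
- Typical t ≈ 20.5/12.9 = 1.6, against a critical value of 2.01.

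**Simulated probability that ALT is significant.**

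| KD patients at 200 | t test | t on logs | rank-sum | ANCOVA | ANCOVA on logs |
|---|---|---|---|---|---|
| 3 of 24 | 20% | 14% | 8% | 20% | 15% |
| 4 of 24 | 43% | 23% | 13% | 44% | 25% |

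With no affected patients the rates are about 5%, as they should be.

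**Sodium.** With 3 patients at 125 and 3 at 155, the shift in the mean is (3 × (−15) + 3 × 15)/24 = 0. Simulated detection is about 0% by t test and ANCOVA and 1.2% by rank-sum. With 3 patients at 125 and none high, the t test still misses the problem in about 81% of trials.

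**Other assumed inputs.** With ALT at 300, median 40 and log-SD 0.4 to 0.6, two or three affected KD patients leave the marker non-significant in 79% to 97% of trials; four leave it so in 39% to 87%. Balanced sodium shifts (124 and 154, one to four patients each way) are missed in 97% to 100%.

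**What counts of patients would show.** Expected numbers are 3 + 21p (KD) and 24p (SD) for ALT with 3 affected. For low sodium in the 3 + 3 case they are 3 + 18p and 24p. Here p is the unaffected proportion beyond the limit.

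| Limit (assumed) | p | KD | SD |
|---|---|---|---|
| ALT > 40 | 31.6% | 9.6 | 7.6 |
| ALT > 55 | 15.6% | 6.3 | 3.7 |
| ALT > 120 (3 × 40) | 1.0% | 3.2 | 0.2 |
| ALT > 165 (3 × 55) | 0.2% | 3.0 | 0.1 |
| Sodium < 135 | 4.8% | 3.9 | 1.1 |
| Sodium < 130 | 0.04% | 3.0 | 0.0 |

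By symmetry, high sodium (above 145 and above 150) gives the same counts. The severity level separates the arms much better than the normal limit does. Such a table remains descriptive: 3/24 (exact 95% CI 2.7% to 32.4%) against 0/24 (0% to 14.2%) has Fisher p = 0.23.

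**The case against.** **Individual harm is covered elsewhere.** Laboratory results are reviewed every 3 months by a committee with two external monitors, and adverse events are reported. Planned variances and box plots could also hint at trouble: the median KD/SD variance ratio is 7.7 for ALT (3 affected) and 7.5 for sodium (3 + 3). This stands as protection of participants and is why the point is not graver. None of it enters the stated conclusion, and none of it provides a between-arm comparison of abnormal patients.

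**The detail belongs in the analysis plan.** Shift tables and severity grades usually do. Here, though, the article positively sets established safety values aside and says what will be concluded without them. That is a stated choice. The sentence could be read as rejecting only a comparison of each group's level with a reference, so a change of conjunction alone would not suffice; the patient-level table has to be named.

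**The rates are not those of the whole rule.** Correct. If all markers must be non-significant, 14 independent null markers (excluding β-hydroxybutyrate) would all pass in only 0.95¹⁴ = 49% of trials. The diet is also meant to raise β-hydroxybutyrate, so a literal reading would rarely allow the safe conclusion. That makes the rule erratic. It does not make it sensitive to the affected patients, and marker by marker the weakness remains.

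**The sodium case is extreme.** The near-zero figure needs near-balance: t-test detection is 0.4% for a 4/2 split, 15% for 5/1 and 74% for 6/0. This is fair, and the example is illustrative. The one-directional case of three patients is still mostly missed.

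**Conclusion.** The point holds and should be corrected. As written, safety on the first-listed primary outcome is concluded from tests of group level, with comparison against established limits set aside. For a single affected marker with 24 per arm, three severely abnormal KD patients would go undetected in roughly 80% to 92% of trials under the main ALT assumptions; opposite sodium shifts of equal size would almost never be detected.

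The percentages depend on assumed distributions and on how many patients are affected: with four at ALT 200, the t test or ANCOVA detects the problem in just over 40%. The cancellation for sodium follows from symmetry whatever the SD. The conclusion concerns the published safety statement, not the monitoring of participants during the trial.

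**What to change.** Rewrite the sentence in Statistical analysis so that comparison with laboratory limits is made *in addition to* the comparison of group levels, and say that it is made patient by patient:

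- For each safety marker, tabulate by arm the patients whose worst post-baseline value (rehabilitation or discharge draw) lies beyond the laboratory's limits.
- Do this at the normal limit and at standard severity levels named before unblinding, for example multiples of the upper limit for liver enzymes. Show low and high sodium separately.
- Show the shift from the baseline category, so that abnormality due to the trauma itself is visible in both arms.
- Give exact 95% confidence intervals for the proportions and for their difference.
- Base the safety statement on these tables together with the intervals for mean differences, and drop the inference from non-significance.

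The cost is one rewritten sentence, one table per marker from data already collected, and severity levels chosen in advance. Small counts will give wide intervals, so the safety statement will be less firm.

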### Power calculations

Power calculations were performed using nQuery Advisor + nTerim 3.0, and assume a two-sided statistical test and a significance level of 5%. We obtained estimates of the standard deviation for the motor score of 23.5 and for the light touch score of 33 (both based on our preliminary data). With a final sample size of 24 participants per group, and also assuming a two-group *t* test and the prior assumptions, we have 80% power to detect between-group differences of 19.5 in the motor score and 27.3 in the light touch score as being statistically significant. With a final sample size of 24 participants per group, and assuming a paired *t* test and the prior assumptions, we have 80% power to detect within-group changes of 14.1 in the motor score and 19.8 in the light touch score as being statistically significant. All of these differences are approximately at the same levels as those that Kramer et al. detected as being statistically significant and clinically meaningful [36]. We believe that these estimates are conservative since we are performing our primary statistical analyses for between-group and within-group comparisons simultaneously using statistical methods that are more sophisticated than those that are assumed here. Given our history in SCI patient recruitment and the large SCI patient base at the UAB SRC, we fully expect to meet our recruitment goal.

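### Non-significance on laboratory markers at 24 per arm cannot establish that the ketogenic diet is safe, and the rule conflicts with the protocol's own ketosis target

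*Protocol article*

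**What the plan says.** Showing safety is the first goal in the Abstract and Background, and safety is the first primary outcome under Outcome measures and analysis. It is defined there by laboratory measures only: C-reactive protein, four lipids, sodium, six liver measures, beta-hydroxybutyrate, fasting glucose and insulin.

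The Statistical analysis section says how these will be judged. The arms are compared with each other at the assessment times, "instead of comparing the two groups to the established standard safety values". The decision rule follows: "If there are no significant group differences in these outcomes, we will conclude that the KD intervention is safe". The next sentence adds "95% confidence intervals for the mean group differences for these outcomes as an additional check on safety and feasibility", without saying which interval would overturn the conclusion. The same section makes ANCOVA with baseline adjustment the primary method, names safety among its outcomes, and sets the error level: "Statistical tests will be two-sided and will be performed using a 5% significance level".

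Power calculations covers the motor and light touch scores only. No safety marker has an SD, a margin or a stated power.

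Clinical procedures to measure safety says that blood ketones are measured to confirm ketosis at 0.5–3.0 mM in the ketogenic diet (KD) arm.

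Adverse events are handled elsewhere. Under Data management, "data on adverse events that are collected by the medical team are recorded on paper forms" and then entered in the database. Trial monitoring has a committee with two external monitors review them every three months, and Annual reports compares their rates with expected rates. None of this is linked to the final safety conclusion.

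**The concern.** The rule takes failure to reject a null of no difference as proof that the null is true. The smaller or noisier the trial, the easier it is for a harmful shift to go undetected. It also errs the other way: many markers are each tested at 5%, so a diet without effect can fail by chance.

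The confidence intervals could repair this only if there were a limit to read them against, and there is none. Since established safety values are set aside as well, nothing ties the verdict to the size of a harm.

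The answer to the first goal is at stake. The Discussion looks ahead to a diet that could be adopted widely, so an unsupported safety claim would carry weight.

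**Working it through.** **Inputs.** 24 per group and two-sided 5% (Power calculations: "assume a two-sided statistical test and a significance level of 5"%; the same level in Statistical analysis). Motor SD 23.5, light touch SD 33. Fifteen safety markers: 1 + 4 + 1 + 6 + 1 + 2. Assumptions, because the article gives no figures for them: harms in SD units, baseline correlations of 0.5 and 0.7, and between-marker correlations of 0 to 0.5.

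**1. The plan's own figure.** Two-sample t test, df = 46, noncentrality d × √(24/2). Motor: d = 19.5/23.5 = 0.83, power 80.3%. Light touch: d = 27.3/33 = 0.83, power 80.1%. The stated 80% is reproduced, so the same formula is used below.

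**2. One marker.** Chance of a non-significant result. For ANCOVA, d is replaced by d/√(1 − r²), with df = 43 (48 less intercept, diet, baseline, age and sex).

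| True shift | Unadjusted | ANCOVA, r = 0.5 | ANCOVA, r = 0.7 |
|---|---|---|---|
| 0.3 SD | 83% | 78% | 70% |
| 0.5 SD | 60% | 50% | 34% |
| 0.8 SD | 23% | 12% | 3% |

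The shift missed half the time is 0.58, 0.50 and 0.41 SD respectively. The unadjusted 95% interval has half-width t(0.975, 46) × √(2/24) = 2.013 × 0.289 = 0.58 SD.

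**3. All markers together.** The rule speaks of the outcomes jointly, so one significant marker blocks the verdict. Leave out beta-hydroxybutyrate (step 4), which gives 14 markers, one test each, unadjusted.

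- No effect on any marker, independent: 1 − 0.95^14 = 51% chance of at least one significant difference. Simulated at common correlation 0.3 and 0.5: 44% and 35%.
- 0.5 SD harm on one marker, independent: 0.604 × 0.95^13 = 0.604 × 0.513 = 31% declared safe. Simulated at correlation 0.5: about 41%.
- 0.3 SD harm on one marker: 0.826 × 0.513 = 42% independent; about 57% to 58% at correlation 0.5.
- 0.8 SD harm on one marker: 0.226 × 0.513 = 12% independent; about 12% to 13% at correlation 0.5.

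At independence the verdict of safety is thus given to 49% of trials of a harmless diet and 31% of trials with a 0.5 SD harm. At correlation 0.5 the figures are 65% and 41%. The rule separates the two cases poorly. Testing at several time points would change these figures and is not counted.

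**4. Beta-hydroxybutyrate.** It is on the safety list, and the KD arm is meant to be in ketosis. A diet that works as intended should differ from the standard diet on this marker and so fail the literal rule.

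**5. What a margin rule could deliver at 24 per arm.** With no true difference, the chance that the harmful-side limit of the 95% interval lies inside a margin of m SD is Φ(m/√(2/24) − 1.96): m = 0.3: Φ(1.04 − 1.96) = 18%; m = 0.5: Φ(1.73 − 1.96) = 41%; m = 0.8: Φ(2.77 − 1.96) = 79%; m = 1.0: Φ(3.46 − 1.96) = 93%.

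**6. Events.** Zero events among 24 KD participants leaves an exact two-sided 95% upper limit of 1 − 0.025^(1/24) = 14%.

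**The case against.** A reader might infer that a real harm would usually be certified as safety. The documents do not support that. The 60% miss rate is for one marker and an unadjusted test, whereas the rule covers the outcomes jointly and the primary analysis is ANCOVA. Jointly, a 0.5 SD harm on one marker is passed in fewer than half of trials, and a 0.8 SD harm is usually detected even on a single unadjusted test. Only a small harm (0.3 SD) with correlated markers is passed more often than not.

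The 35% to 51% is not a clean false-alarm rate either. Better glycemic control is an aim of the trial, so a difference in glucose or insulin might be benefit. The figure describes a diet that changes none of the 14 markers.

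A reader might also infer that adverse events are neglected. They are recorded, reviewed quarterly with external monitors, and reported to the IRB and NIH/NINR. Event tables by arm are something an article may leave to the fuller documents, so their absence here is not an error. What stands is narrower: the article states how safety will be concluded, and that statement does not include events.

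Finally, the interval sentence could be read as a safeguard. It would be one if it had a criterion; as written, no interval can change the verdict.

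**Conclusion.** The rule is wrong as written and should be changed before any comparison by arm. This is stated text, not detail left to an analysis plan. Non-significance at 24 per arm cannot establish safety: a 0.5 SD shift on a given marker is missed in about 60% of trials unadjusted, or 50% to 34% under the assumed ANCOVA gains. Under the joint reading the verdict depends heavily on chance: about 31% to 41% of trials with a 0.5 SD harm on one marker are called safe, and about 35% to 51% of trials of a diet without effect are not. Including beta-hydroxybutyrate sets the rule against the protocol's own ketosis target.

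The sizes rest on assumed standardized shifts and correlations, one test per marker, and 24 completers per arm. The flaw in the logic does not depend on them.

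**What to change.** - Delete the sentence that infers safety from non-significance.
- Take beta-hydroxybutyrate out of the no-difference comparison and report it as a measure of ketosis and adherence.
- For each remaining harm marker, have the study physician and the external safety monitors state the largest acceptable difference between arms, and its direction, before results by arm are seen.
- Base the safety statement on the 95% intervals already planned, together with adverse and serious adverse events by arm.
- Use the wording *no relevant harm* only for a marker whose interval excludes its margin. Otherwise write *no difference shown* and give the interval.

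The cost is a change of wording and a table of margins, with no new data. The downside is real: with no true difference, 24 per arm excludes a 0.5 SD margin only about 41% of the time and a 0.8 SD margin about 79% (unadjusted; baseline adjustment would help somewhat). For many markers the trial will report an estimate with its interval and will not be able to say *safe*.
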